## Abstract

**Background:**

HIV and Hepatitis C (HCV) are blood borne infections (BBIs) that remain a significant cause of global morbidity and mortality among people who inject drugs (PWID). UNAIDS and WHO have set goals for the elimination of viral hepatitis and HIV as major public health threats by 2030. To achieve these targets, innovative strategies are required among marginalized populations such as PWID, especially in resource-limited countries where coverage of harm reduction services is often limited. The goal of this study is to inform targeted strategies to prevent transmission of BBIs among PWID.

**Methods:**

We will use respondent driven sampling (RDS) to recruit PWID from needle and syringe programs in Kenya. Participants will complete biobehavioral and social network surveys and receive point-of-care HCV, HIV, and hepatitis B (HBV) testing. Participants will return for at least one follow-up visit to complete additional surveys and testing. We will use network data from RDS, egocentric, and viral phylogenetics to identify how highly central PWID contribute to transmission networks and use mathematical modelling to investigate the impact of targeted interventions based on network characteristics.

**Discussion:**

This study will provide important information for policymakers and researchers designing strategies for BBI elimination. Network- and molecular epidemiologic-informed tools to guide targeted strategies may be critical to maximizing the impact of treatment and prevention efforts in resource-limited settings. This approach may provide a durable template for future studies, including prospective assessments of targeted prevention and elimination strategies among PWID, and assist with monitoring elimination progress in resource-limited settings.

## Introduction

There are approximately 14.8 million people who inject drugs (PWID) worldwide, with an estimated 38.8% (or 5.8 million) living with hepatitis C (HCV), 15.2% (or 2.3 million) living with HIV, and 8.4% (or 1.2 million) living with hepatitis B (HBV) [1]. Between 2010 and 2022, annual new HIV infections among PWID decreased by 24% [2]. This is a significant improvement from data from 2016 indicating rising incidence among PWID [3]; however, risk of HIV acquisition among PWID remains 14 times higher than the general population [4]. People living with HCV and HBV are at risk of progression to liver cirrhosis, hepatocellular carcinoma, and liver failure [5]; without effective treatment and prevention interventions, 19 million global viral hepatitis-related deaths are expected by 2030 [6].

HIV prevalence among PWID in Sub-Saharan Africa is lower than the global prevalence (11.2% Sub-Saharan Africa, 15.2% global), and HCV prevalence among PWID in Sub-Saharan Africa is low (20.6% Sub-Saharan Africa, 52.5% global) [1, 5]; however, an increasing number of PWID live with and are becoming HIV- and HCV-infected in this region. Additionally, direct-acting antiviral (DAA) treatment for HCV in many African countries is limited [6, 7] and antiretroviral therapy (ART) uptake for HIV among PWID has been challenging [8, 9]. As such, targeted public health strategies may be an important way to increase the efficiency of preventing transmission of HIV, HCV, and other blood borne infections (BBIs) among PWID in Sub-Saharan Africa. Commonly applied strategies based on evidence from predominantly European and North American settings may not meet the needs of populations in Sub-Saharan Africa due to infrastructural challenges, delays in scale up, or sub-optimal coverage [2, 7, 10]. The implications of delayed treatment and prolonged HIV and HCV viremia in a population with high risk for community transmission is alarming and underscores the need for systematic surveillance and interventions in the context of comprehensive health service delivery systems. However, HIV and HCV surveillance and infrastructure for intervention are underdeveloped in many LMICs, particularly among marginalized populations like PWID.

Conservative estimates place approximately 36,000 PWID in Kenya [1, 11]. Among this population, HCV prevalence has recently been estimated to be 1% in the Western region, 13% in Nairobi, and 22% in the coastal region [12]. The geographic gradation in HCV prevalence is likely attributable to relatively new access to heroin beginning in the 1980s associated with a tourism boom on the Kenyan coast, which gradually spread inland [13]. Kenya introduced needle and syringe programs (NSPs) and opioid agonist therapy (OAT) as part of a nationwide HIV prevention strategy in 2012 and 2014, respectively [13]. NSP sites provide PWID-specific services in line with the WHO recommended programming, including needle and syringe exchange, HIV testing and counseling, HIV treatment and care, prevention and treatment of sexually transmitted infections, and condom distribution, among other services [14]. OAT sites dispense medication for opioid use disorder and provide other services like education and treatment planning, laboratory monitoring, individual and group therapy, and referrals to other services [15]. A recent analysis found that OAT and NSP usage conferred benefits on several different HIV-related outcomes; OAT access was associated with increased ART coverage and viral suppression, and NSP access was associated with lower HIV incidence [16]. The Government of Kenya published its first viral hepatitis guidelines and committed to scaling up DAA therapy in 2017, and have identified PWID as a priority population [17]. Initial data on treatment outcomes among PWID are promising [18, 19]. Modeling data indicate that scale-up of DAA coverage in combination with harm reduction interventions could reduce HCV incidence in Kenya by 90% by 2030 [20], and that DAA treatment for PWID can be cost-effective [21].

Despite the successful implementation of these programs, challenges remain [22]. A recent global systematic review found that Kenya had fairly low NSP and OAT coverage relative to the number of PWID in the country [23] and funding gaps for these harm reduction programs pose obstacles to consistency of care provision and opportunities to expand services [24]. Additionally, challenges with availability and access to commodities for testing and treatment, and financial and policy barriers pose obstacles to greater DAA scale-up and uptake [10]. Recent funding cuts to global health organizations have also drastically impacted clinics and drop-in centers offering HIV and HCV care, substance use disorder treatment, and harm reduction services [25–27].

Social network characteristics play an important role in HIV and HCV transmission among PWID [28–32]. Factors like network size, composition and characteristics, and density have been shown to be associated with multiple behaviors associated with both HIV and HCV risk, including sharing of needles/syringes and other injection paraphernalia [33]. Individuals’ positions within a social network can also be ranked using different measures of centrality such as degree, closeness, betweenness, and Eigenvector centrality. Highly central positions (i.e., being highly-connected at the center of a network) have been linked with HIV and HCV infection, as well as risky injection and sexual behaviors [31, 34, 35]. Little network simulation research has been conducted in Sub-Saharan Africa, and it is unclear how generalizable findings from other settings may be to Sub-Saharan Africa, warranting further investigation in the region.

Geographic factors related to transmission networks also influence HIV and blood borne infection risk. For example, settings of care and harm reduction services, as well as locations of injection hotspots and places to purchase drugs influence BBI risk and transmission [36]. Evidence from studies in other settings indicate that while social network analyses alone may be helpful in identifying individuals for HIV and HCV treatment and reducing community viral load [37], geospatial analyses should also be considered, as BBI transmission may also be clustered at certain locations which could then be targeted for venue-based interventions [29, 30, 32]. Preliminary analyses from our study have also shown geographic variations in social network characteristics [38], further highlighting the need for continued investigation of socio-spatial networks among PWID in Sub-Saharan Africa.

The high transmissibility and genetic diversity of HCV can be leveraged to better understand BBI transmission networks among PWID, as similarity between strains is indicative of transmission linkages. Phylogenetic analyses can be used to model historical relationships between infected individuals and identify individual and geospatial characteristics that account for transmission [39, 40]. Understanding HCV transmission networks allows for identification of PWID who are most likely to receive and transmit HCV and other BBIs. The 2014 HIV outbreak in Scott County, Indiana, in which a cluster of 11 HIV-positive PWID grew to 181 cases within one year [41, 42], demonstrates how understanding of high centrality PWID within injection networks is critical to informing prevention efforts. Over half of the recently HIV-infected PWID in this outbreak belonged to the largest HCV transmission cluster; a better understanding of this transmission network could have been used to better inform prevention strategies that could have prevented this HIV outbreak [41, 42]. Incorporating phylogenetic analysis into traditional social network analyses expands upon existing understanding of transmission relationships and provides additional empirical information on transmission linkages. Social network and phylogenetic analysis can be used in tandem to identify and rank nodes (i.e., individuals) according to various measures of centrality [43]. Identification of central individuals using multiple network measures could be used to more effectively target interventions and to investigate additional factors associated with high centrality.

## Methods

### Study Objectives

The primary aim of the study is to characterize PWID networks, including HCV transmission networks, and identify high centrality PWID. We also aim to determine demographic, behavioral, virologic, and geographic risk factors associated with highly central PWID. We hypothesize having a highly central position will be associated with the greatest risk of HIV and HCV. Furthermore, we will develop mathematical models to examine population-level effects of targeted, network-based interventions to reduce transmission of HIV, HCV, and other BBIs.

### Study Design

We will use respondent driven sampling (RDS) to recruit PWID in Coastal Kenya, Nairobi, and the Western Region. RDS was chosen because it is useful in reaching “hidden” populations and can overcome biases of traditional snowball sampling [44–47]. Additionally, RDS represents one means of understanding connections between participants and is thus useful in finding highly linked people.

### Study Settings

Study settings mirror those of the Testing and Linkage to Care for Injection Drug Users in Kenya (TLC-IDU) study (NCT01557998) [12, 48], which leveraged the emergence of harm reduction programs in Kenya to identify, test, and link PWID to HIV and HCV care, and demonstrate the benefits of these interventions [16]. This study will provide continuity by linking participants from harm reduction to HIV and HCV care, but data collected in this study will also be used to inform new models and strategies for treatment and prevention of BBIs in PWID.

#### Needle and Syringe Programs (NSPs)

We will recruit RDS seeds from and conduct visits at 17 NSP sites in Coastal Kenya (N=8; 3 Mombasa, 3 Kilifi, and 2 Kwale), Nairobi (N=5; 4 Nairobi and 1 Kiambu), and the Western Region (N=4, 1 Kisumu, 2 Migori, and 1 Kisii). NSPs provide injection harm reduction kits (consisting of alcohol swabs, sterile water, sodium hypochlorite solution, and citric acid powder); employ peer educators/navigators who demonstrate safe injection practices, risk-education counseling, and safer sex education; and utilize peer case managers who follow up on individuals who are HIV- and/or HCV-positive. Specified care providers at NGOs in all three study regions have also been engaged to provide PWID-specific services. These sites participate as NSPs and link clients with additional services. The peer navigators maintain a log of all services received by clients in collaborating facilities as per facility protocol, allowing them to track ART, DAA, and other service uptake.

### Study Population and Sampling

We will enroll up to 3500 PWID in Coastal Kenya, Nairobi, and the Western Region. Biometric data capture using iris scanners will be used to prevent double enrollment and to track repeat visits. Participants who test HIV-positive and/or HCV antibody-positive will be eligible to complete up to three follow-up visits in the year following their baseline visit. Additionally, participants who test HIV-negative and HCV antibody-negative will complete a one-time follow-up visit to assess for seroconversion. For each visit, participants will be compensated 400 KSH.

To perform RDS sampling, study and NSP staff will identify individuals who are highly socially networked to serve as seeds and begin peer recruitment chains. Between two and six initial seeds will be recruited from each NSP site. Potential seeds will complete a brief interview with study staff, after which seeds will be selected based on the number of other PWID they know and associate with, previous testing access and results, and length of time spent in each area/neighborhood. Once consented by research staff, these seeds will be instructed on how to recruit up to three eligible peers and offer them a coupon that allows study staff to track recruitment relationships. If the potential recruit approaches study staff with the coupon and expresses interest in participation, they will be screened and consented for the study. Potential recruits need not already be clients at the NSP site at which they redeem the coupon. Participants who recruit their peers will receive 100 KSH for each successful referral.

After enrollment and once all three coupons are distributed, each participant will be provided with up to five tokens and instructed to give these tokens to individuals who they know are already enrolled in the study. Tokens will be used to establish connections between existing study participants, compared to coupons which only allow participants to recruit peers who are not already enrolled in the study. Tokens will allow for better understanding of network connections than the limited tree-structures available in RDS. Individuals who are retained for the follow-up cohort will receive up to eight follow-up tokens to distribute at each follow-up visit. When participants redeem tokens, they will complete a brief survey and receive payment. Participants who provide another participant with a token will receive 50 KSH upon the token’s successful redemption; those redeeming the token will receive 100 KSH. Tokens will allow for visualization of how network members change or stay the same over the study period.

Subjects who are unable to recruit peers will be asked to return their unused coupons (a “buy-back” process, 50 KSH per unredeemed coupon) at the end of each recruitment period. They will participate in a short interview asking about their experience trying to recruit peers and reasons why they were unable to recruit peers. Similarly, participants whose tokens are not redeemed will also complete a buy-back process involving a short survey with questions on how many tokens were given out, whether any tokens were refused, by whom, and what the reasons for refusal were. Participants will receive 20 KSH per token in the buy-back process.

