### Additional Planned Analyses

Baseline and follow-up demographic and clinical information will be used to assess demographic, behavioral, structural, virologic, and geographic risk factors associated with positions of high centrality; additionally, we will assess associations between centrality measures and HIV, HCV, and HBV disease status. To assess centrality, we will create a unified network using egocentric social network data, RDS data, and token data; and use results from the GHOST analysis to examine how transmission occurred within these other networks. Tabular analysis will be used to explore bivariate associations between these characteristics, risk behaviors, and the presence of HIV/HCV co-infection or multiple-strain HCV infection. Factors strongly associated with having high centrality with *p*-values less than 0.2 will be considered for inclusion in multivariable models. Because RDS sample is not a random sample, we will conduct weighted regression analyses by using RDS weights, which are calculated as inverse of self-reported network size [64].

To evaluate the effect of having high centrality on transmission and acquisition of blood borne infections, cox proportional hazard models (adjusting for host demographic, risk behavior and clinical factors) will be used to estimate the hazard ratios for associations between HIV/HCV co-infection, multiple-strain infection, and other factors associated with having high centrality on the probability of incident blood borne infections. Incidence rates per 100 person-years of HIV and HCV were estimated to be 2.5 and 6.3 in the coastal region, 1.6 and 2.3 in Nairobi, and less than 1 in the Western region, based on previous data [12].

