## Limitations

The assertion that individuals who are highly central will be at high risk of receiving and transmitting HIV, HCV and other BBIs may not be evident in this population of PWID. Moreover, the association of HIV/HCV co-infection, multiple-strain HCV infection, or other factors may not be able to be demonstrated in this sample due to sample size constraints. Additionally, though we believe RDS to be the best sampling method for this work, it may also introduce some bias to the study. For example, though RDS assumes recruiters will pass their coupons and tokens to network contacts, it is possible that they may pass the coupon off to a stranger (e.g., someone visiting the NSP site at the same time). Coupon distribution behaviors (e.g., who is approached, why and how they are approached, who accepts and why they accept) may also vary between individuals, leading to undocumented variation. In highly clustered populations, it is also possible that the RDS sample will not mix well and draw from the full target population with the expected proportions. This could lead to undue influence of the seeds on the final sample. This method of recruitment by referral also naturally biases selection towards individuals with a larger number of contacts. Individuals with no contacts will not be represented in the sample. Additionally, given that each referral chain starts at a single location, the geographical distribution cannot be expected to be representative of the whole population of PWID. PWID living close to a seed location are more likely to be included. Additionally, those living far away from an NSP site may be less likely to return a coupon.

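### Seeds are chosen partly on network size and partly on previous test results, and the stated weight does not correct for that, so analysing them as ordinary participants can bias the cross-sectional centrality-infection association

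*Protocol article*

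**What the plan says.** Under Study Population and Sampling, "study and NSP staff will identify individuals who are highly socially networked to serve as seeds and begin peer recruitment chains". After a brief interview, "seeds will be selected based on the number of other PWID they know and associate with, previous testing access and results", and also on time spent in the area. On numbers, "Between two and six initial seeds will be recruited from each NSP site"; the section on needle and syringe programs gives 17 sites, and the ceiling is stated as "We will enroll up to 3500 PWID in Coastal Kenya, Nairobi, and the Western Region". Seeds give consent and start the coupon chains.

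Under Additional Planned Analyses, "we will assess associations between centrality measures and HIV, HCV, and HBV disease status". The regressions are to use "RDS weights, which are calculated as inverse of self-reported network size". No separate rule for seeds is given.

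The HCV, HIV and HBV testing sections test at baseline only participants without a registry result from the prior three months. Positive Cohort Follow-Up treats a recent recorded positive as equivalent to a positive baseline test.

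Limitations says of seeds: "This could lead to undue influence of the seeds on the final sample". That sentence concerns chains that mix poorly; it does not refer to selection on test results.

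**The concern.** The study's hypothesis is that highly central people carry the greatest HIV and HCV risk. One identifiable group enters the sample partly because of something close to the exposure and partly in view of something close to the outcome. For a seed with a recent registry result, the result seen at selection may be the very baseline status that is analysed.

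Inverse-network-size weights rest on recruitment through peers with probability proportional to network size. Seeds enter by staff choice, so the weight is not their inverse inclusion probability, and it carries no information about test results. Seeds are few overall, but having been picked as well connected they may form a much larger share of the high-centrality group, where a distortion would show.

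**Working it through.** The article gives no power or sample-size calculation, so there is no figure of the plan's own to reproduce. The site count is consistent: 8 + 5 + 4 = 17.

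**Number of seeds.** 17 × 2 = 34 and 17 × 6 = 102. As shares of 3,500: 34/3,500 = 1.0% and 102/3,500 = 2.9%.

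**Inputs from the article.** HCV prevalence of 22% on the coast, 13% in Nairobi and 1% in the Western region (Introduction); enrolment of 3,500.

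**Assumptions not in the article.** High-centrality share among non-seeds of 10% (20% and 50% as alternatives); all seeds classed as high centrality; self-reported network size of 12 for high-centrality recruits, 4 for the others and 20 for seeds, giving weights 1/12, 1/4 and 1/20; seed positivity *q* varied. The true odds ratio among recruits is set to 1.

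**Formula.** With *S* seeds, *n* = 3,500 − *S*, prevalence *p* and high share *h*:
- weighted high-centrality positives: *a* = *n·h·p*/12 + *S·q*/20
- weighted high-centrality negatives: *b* = *n·h*·(1 − *p*)/12 + *S*·(1 − *q*)/20
- odds in the low group: *p*/(1 − *p*)
- OR = (*a*/*b*) ÷ [*p*/(1 − *p*)]

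**Worked cases at p = 0.13, h = 0.10** (low-group odds 0.13/0.87 = 0.1494):
- *S* = 34, *q* = 0.26: *a* = 3.755 + 0.442 = 4.197; *b* = 25.129 + 1.258 = 26.387; odds 0.1591; OR 1.06.
- *S* = 102, *q* = 0.50: *a* = 3.681 + 2.550 = 6.231; *b* = 24.636 + 2.550 = 27.186; odds 0.2292; OR 1.53.

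| Seed positivity | Weighted OR, 34 seeds | Weighted OR, 102 seeds |
|---|---|---|
| 0% (positives avoided) | 0.94 | 0.83 |
| 13% (same as recruits) | 1.00 | 1.00 |
| 26% (doubled) | 1.06 | 1.18 |
| 50% | 1.19 | 1.53 |

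The 0% row uses the same formula: 3.755/26.829 = 0.1400, OR 0.94; 3.681/29.736 = 0.1238, OR 0.83.

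**Wider range.** Over 13% or 22% prevalence and high shares of 10% to 50%, the weighted OR is 1.01 to 1.20 if seed positivity is doubled and 1.02 to 1.53 if it is 50%. Unweighted, the ranges are 1.02 to 1.32 and 1.03 to 1.84. The weights therefore shrink the seeds' influence but do not remove it.

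**Type I error.** In 4,000 simulations per scenario at 13% prevalence, with high shares of 10% and 20%, a nominal 5% weighted test rejects in 5% to 19% of cases if seed positivity is doubled and 11% to 88% if it is 50%. With seed positivity equal to that of recruits it stays at about 5%.

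**If only half the seeds rank high** (*S* = 102, *q* = 0.50), the other 51 move to the low group: *a* = 3.681 + 1.275 = 4.956; *b* = 24.636 + 1.275 = 25.911; low-group odds (99.392 + 1.275)/(665.159 + 1.275) = 0.1511; OR = 0.1913/0.1511 = 1.27 instead of 1.53.

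**Western region.** Four sites give 8 to 24 seeds. With enrolment in proportion to sites and 1% prevalence, the weighted OR is 1.03 to 1.15 if seed positivity is doubled to 2%, and 2.4 to 9.2 if half the seeds are positive (high shares of 10% and 20%). The second case is extreme; it shows how little it takes to move an estimate where positives are rare.

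**The case against.** The strongest reply is that two links are not in the text. First, the article never says outright that seeds enter the centrality-infection models; a condensed article may leave this to an analysis plan. Second, it does not say how test results are used: positives may be favoured, avoided or balanced, and which infection is meant is not stated. A reader might infer that the design necessarily builds in a positive association. The documents do not support that: the sign is unknown, and the bias is nil if seed positivity equals that of recruits.

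A reader might also infer a larger effect from an unweighted calculation. The plan is for weighted regression, and people selected for large networks receive small weights. Nor need all seeds rank high: centrality comes from a unified network of survey, coupon and token data, and in the coupon tree a seed has at most three ties while a recruit can have four (three coupons plus the recruiter).

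Finally, one could argue for dropping seeds from every model. That goes too far. Describing high-centrality people is part of the primary aim, and past results do not select in the same way on later seroconversion among people negative at baseline.

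These points limit the size and certainty of the bias. They do not remove the mismatch between two things the article does fix: a seed criterion that includes test results, and a weight that cannot correct for it. Seeds are enrolled participants and nothing sets them apart in the analysis. The acknowledgement in Limitations concerns poor mixing, a different mechanism.

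**Conclusion.** The point holds as a risk of bias of unstated direction in the cross-sectional models of centrality and HIV, HCV or HBV status. In the pooled sample it is small to moderate: with no true association, a weighted OR of about 1.0 to 1.2 if seed positivity is doubled and at most about 1.5 if it is 50%, and below 1 if positives are avoided. It could be larger in the low-prevalence Western region. These figures rest on the assumed network sizes, centrality cut-off, seed positivity and ranking of all seeds as highly central, and on seeds being modelled as ordinary participants. The Cox incidence models are less directly affected. It is worth correcting because the seeds can be identified from the recruitment records and the remedy is cheap.

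**What to change.** 1. State how previous test results enter seed selection: which infections, and whether positives are favoured, avoided or balanced.
2. Flag seed status in the data set. Keep seeds as nodes when the network is built and when centrality is computed and described.
3. Fit the cross-sectional models relating centrality to baseline HIV, HCV and HBV status without seeds, or with a seed indicator. Report the version with seeds included as a sensitivity analysis.
4. In the Cox incidence models keep seeds, and add a sensitivity analysis without them.

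The cost is a few sentences in the plan. If seeds are excluded, the cross-sectional association models lose 1% to 3% of participants. The loss from the high-centrality group could be larger: if all seeds rank there and the share among non-seeds is 10%, it is 34/(346.6 + 34) = 8.9% to 102/(339.8 + 102) = 23.1% of that group, with some loss of precision. A seed indicator avoids dropping anyone.

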#### Positive Cohort Follow-Up

Participants who test HIV- or HCV antibody-positive at baseline or had a recent positive test recorded will undergo three follow-up visits at four-month intervals in the year following their baseline visit. Participants are given a one-month grace period before and after the four-month mark in which they can complete the visit. Participants who miss a visit are still eligible to complete later follow-up visits. Peer case managers at each site will assist study staff with recalling participants for their follow-up visits by conducting outreach at commonly frequented injection venues. At each of the three follow-up visits participants will complete biobehavioral and social network surveys with updated time frames, and will receive HIV, HCV, and HBV testing.

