#### Negative Cohort Follow-Up

Due to resource limitations, it will not be possible to conduct multiple follow-ups for all participants. Following completion of the positive cohort follow-up visits, we will conduct one additional follow-up visit for individuals who test HIV- and HCV antibody-negative during their baseline visit to determine seroconversion with HIV, HCV, and/or HBV. Biobehavioral and social network data will also be collected during these follow-ups.

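### HIV- or HCV-positive participants get more token and survey rounds than negatives; unless centrality is confined to a common wave, this alone makes them look more central

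*Protocol article*

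**What the plan says.** Under Study Population and Sampling in the protocol article, at enrolment "each participant will be provided with up to five tokens". Later, "Individuals who are retained for the follow-up cohort will receive up to eight follow-up tokens to distribute at each follow-up visit".

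The number of follow-up visits depends on baseline infection status. The same section says "Participants who test HIV-positive and/or HCV antibody-positive will be eligible to complete up to three follow-up visits in the year following their baseline visit", whereas "participants who test HIV-negative and HCV antibody-negative will complete a one-time follow-up visit to assess for seroconversion". Negative Cohort Follow-Up places that single visit after the positive cohort has finished: "Following completion of the positive cohort follow-up visits, we will conduct one additional follow-up visit".

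The Social Network Survey section allows up to 15 named contacts. Positive Cohort Follow-Up repeats the survey: "At each of the three follow-up visits participants will complete biobehavioral and social network surveys with updated time frames". Negative Cohort Follow-Up also collects social network data at its one visit.

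Under Additional Planned Analyses, "To assess centrality, we will create a unified network using egocentric social network data, RDS data, and token data". The same section relates centrality to HIV, HCV and HBV status. The Recruitment network section says that token data will make the data for estimating centrality more complete. The only stated correction is a regression weight equal to the inverse of self-reported network size.

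**The concern.** A tie is observed only if somebody had the chance to record it. Here that chance is set by baseline HIV/HCV status, which is the variable that centrality is to be tested against. If all waves enter the network, a positive participant accumulates more recorded ties than a negative participant with the same true contacts.

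This bears on the hypothesis in Study Objectives, that a highly central position goes with the greatest risk of HIV and HCV. The artefact points the same way as the hypothesis, so it could be read as support. The weights deal with the probability of being sampled, not with the number of chances to record a tie once enrolled. The Limitations section discusses several recruitment biases but not this one.

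There is a separate timing issue in the incidence models. A participant negative for both viruses has one follow-up visit, the one at which seroconversion is detected. Any follow-up tie which that participant reports or generates by token is recorded at or after outcome detection.

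**Working it through.** **Inputs from the article.** Enrolment tokens: 5. Follow-up tokens per visit: 8. Follow-up visits: 3 (positive) or 1 (negative for both). Names per network survey: 15, at baseline and at each follow-up visit. All are maxima. The article gives no token total or expected centrality difference to reproduce.

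**Opportunity by status.**
- Follow-up tokens: 3 × 8 = 24 against 1 × 8 = 8, a ratio of 3.
- All tokens: 5 + 24 = 29 against 5 + 8 = 13, a ratio of 2.23.
- If the follow-up cohort means positives only: 29 against 5, a ratio of 5.8. The article does not settle this.
- Nominations: (1 + 3) × 15 = 60 against (1 + 1) × 15 = 30, a ratio of 2.

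**Effect on degree when there is no true association.** Simulation was used, with infection independent of the true network. Only the 3,500 participants come from the article. The rest is assumed: 25% in the positive cohort, mean true contacts 8, 15 or 30, token redemption 30% or 60%, and 70% attendance per follow-up visit. The single variations used 15 contacts and 50% redemption. Observed degree is the number of distinct recorded ties, counted for both ends. Central means the top 10% of observed degree.

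| Data used | Mean-degree ratio, positive to negative | Top-decile odds ratio |
|---|---|---|
| Tokens, all waves | 1.11–1.37 | 1.6–2.9 |
| Tokens, all waves, 10% or 40% positive | 1.27 or 1.24 | 2.5 or 2.1 |
| Tokens, all waves, 40% attendance | 1.20 | 2.0 |
| Tokens and surveys, all waves, 30% of names linked | 1.11 | 1.5 |
| Tokens, negatives given none at follow-up | 1.68 | 6.8 |
| Enrolment tokens only | 0.99–1.03 | 0.91–1.11 |
| Enrolment tokens plus one visit for each group | 0.99 | 0.91 |

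Varying the assumptions in further runs gave about 1.9 to 3.2 for tokens alone, and about 1.1 to 2.3 with survey ties added. The latter figure falls as more named contacts can be linked to enrolled people, and rises with true network size. A further run with enrolment tokens plus the baseline survey gave 0.92 to 1.02.

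**Reading the result.** A 29:13 difference in opportunity becomes a much smaller difference in degree. Each tie also counts for the person at the other end, repeat rounds reach the same contacts, and surveys fill in ties that tokens miss. The low end, near 1.1, lies within the simulation noise seen for enrolment tokens (0.91 to 1.11), so with small, well-linked networks the artefact nearly vanishes. No scenario reversed it.

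**The case against.** The strongest reply is that the article never says follow-up ties enter the centrality measure. The sentence on the unified network names sources, not visits. The mention of baseline and follow-up data in the same section concerns demographic and clinical information. Study Population and Sampling also gives tokens a longitudinal purpose, to show how network members change. Which visits define a variable is commonly left to an analysis plan, and that plan is not shown. This stands to the extent that the bias is conditional on pooling. It does not dispose of the point: the article fixes a status-dependent schedule, sends token and egocentric data to centrality without excluding any wave, and names a correction that does not address the problem. An analysis plan that follows this text inherits the bias; one that already restricts the wave needs only to say so.

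A reader might infer more than the documents support:
- **That the schedule alone would confirm the hypothesis.** The plan also compares centrality across data sources, and the phylogenetic network does not depend on tokens or nominations. However, that network covers only participants with sequenced HCV, so it cannot itself compare HCV-positive with HCV-negative people.
- **That an odds ratio of 6 or more is to be expected.** This requires negatives to receive no follow-up tokens, which the text leaves open, and it ignores survey ties.
- **That HBV associations are biased in the same way.** The schedule depends on HIV and HCV antibody status only. Participants positive for HBV alone follow the negative schedule.
- **That unequal schedules bias all incidence analyses.** Participants negative for both viruses share one schedule, whether or not they later seroconvert.

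Only degree was simulated. Closeness and eigenvector centrality, also planned, were not.

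**Conclusion.** The concern holds, conditional on the plain but unstated reading that all waves feed the unified network. The counts (29 against 13 or 5 tokens, 60 against 30 nominations) follow directly from the article and are ceilings. The direction of bias is clear: HIV- or HCV-positive participants look more central through measurement opportunity, and the planned weights do not remove this.

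The size is moderate and uncertain. The spurious top-decile odds ratio is roughly 1.6 to 3 from token ties alone and about 1.1 to 2.3 with survey ties, the latter being closer to the network described. It is larger if negatives get no follow-up tokens, and null with enrolment-wave data. These figures rest on assumed network size, prevalence, redemption, linkage and attendance.

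HBV associations are affected only through HIV/HCV co-infection. In the incidence models the unequal schedule matters only if people already positive for one virus are pooled with those negative for both. The timing problem is separate, and arises only if follow-up ties define the exposure.

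**What to change.** State that the primary centrality measure, for associations with HIV/HCV status and for the incidence models, uses enrolment data only: coupons, the five enrolment tokens and the baseline network survey. Use follow-up tokens and repeat surveys to describe network change, or in a sensitivity analysis that matches or adjusts for the number of token and survey opportunities. State also whether participants negative for both viruses receive follow-up tokens, since the present wording leaves it open.

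This changes analysis wording only; the visit schedule and data collection stay as they are. The cost is fewer observed ties and a somewhat noisier centrality measure.
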